### Subgroup analyses

The following subgroup analyses will be exploratory only. After the main analysis, we will report our key findings by age groups, gender, ethnicity and primary mental health diagnosis. We will investigate whether the treatment effect varies by primary mental health diagnosis or level of learning disability using the LDSQ score. We will repeat the primary analysis and additionally include an interaction term between allocation and primary mental health diagnosis and (in a separate analysis) between allocation and LDSQ score.

We will also conduct an analysis of reliable change for therapy completers (5 out of 7 components of art psychotherapy) using Brief Symptom Inventory Positive Symptom Distress Index (BSI PSDI) scores, allowing for comparison against clinical and non-clinical norms. The Reliable Change Index (RCI) is a psychometric criterion used to evaluate whether a change over time of an individual score (i.e. the difference in BSI PSDI score between baseline and 38 weeks) is considered statistically significant [38]. Firstly, we will identify the RCI on the BSI from baseline (B) to 38 weeks follow-up (F). Participants will be categorised as responders if they see improvement from B to F, neutral if their scores do not change, and deteriorators if their scores worsen. We will repeat the process for MOAS score. To explore the differences between therapy responders and non-responders, we will conduct the primary analysis and additionally include an interaction term between allocation and therapy respondence (responder/neutral/deteriorators). We will explore the demographic/clinical data for the responders and non-responders to compare the profiles.

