#### Secondary objectives

To determine if interpersonal art psychotherapy is cost-effective compared to usual care.To explore patient characteristics and psychotherapeutic processes/mechanisms within interpersonal art psychotherapy that are influential to treatment.To explore the longitudinal changes in aggressive behaviour after receiving art psychotherapy.To evaluate changes in patient distress related to psychiatric symptoms.

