### Sample size

The primary objective is to assess the effectiveness of art psychotherapy in reducing the frequency and severity of aggressive behavior in adult secure care as measured by the Modified Overt Aggression Scale (MOAS) [16]. Based on the results of the feasibility study [11], we assumed a minimum clinically important difference (MCID) of 5 points on the MOAS scale, a common standard deviation of 10 points in the control and intervention groups, and a correlation of 0.25 between the baseline and post-treatment MOAS scores. In addition, we may need to account for clustering by therapist, as a single therapist will apply the intervention to more than one patient. We assumed that each site would have a minimum of 2 therapists and the intraclass correlation (ICC) of the MOAS scores for the same therapist would be 1% in the intervention arm. Under these assumptions, 80% power and a type I error rate of 5%, 59 participants would be required in each arm. To account for an assumed attrition rate of 20%, this figure is inflated to a final sample size of 75 participants per arm, yielding a final sample size of 150 participants.

This would also allow the study to detect a change of 0.5 points on the Brief Symptom Inventory (BSI) Positive Symptom Distress Index (PSDI), used to evaluate changes in patient distress related to psychiatric symptoms [17]. Using an estimated SD of 0.8, the sample size calculated above would result in a power greater than 90% for the BSI comparison.

If the target recruitment (sample size) is not achieved, we will use sensitivity analysis with appropriate statistical methods as planned in the statistical analysis section. If the effect size (i.e. the mean difference of change in MOAS and its standard deviation) differs from our assumptions used in the sample size calculation, this may affect the power/sample size as shown in Table 1.

**Table 1 Tab1:** Potential effects of differing effect sizes and standard deviations on the sample size

Effect size	Power	SD	Method	Correlation (baseline and follow-up)	Alpha	Sample size (per arm)	Final sample size (inc. 20% dropout)
4	0.8	10	ANCOVA	0.25	0.05	92	230
6	0.8	10	ANCOVA	0.25	0.05	41	103
5	0.8	8	ANCOVA	0.25	0.05	37	93
5	0.8	12	ANCOVA	0.25	0.05	85	213

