#### Inclusion criteria

An inpatient in an NHS secure hospital/unit/service with the presence of learning disability/borderline intellectual functioning indicated by either (a) meeting validated assessment criteria (recognised cognitive testing and adapting functioning assessment), or (b) a score of 57 or below on the Learning Disability Screening Questionnaire (LDSQ)Age 18 to 60 yearsAble to give informed consentA current or historic HONOS (Health of the Nation Outcome Scale) score between 1 and 4 for item 1 (overactive, aggressive, disruptive, or agitated behaviour/behavioural problems directed at others)The participants’ involvement in the study is supported by their responsible clinician and/or multidisciplinary team (MDT)

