### Primary outcome

The primary outcome is the frequency and severity of aggressive incidents as measured by the Modified Overt Aggression Scale (MOAS) at week 19 post-randomisation.

The MOAS is completed by a research nurse or clinical support officer at baseline (prior to randomisation), and weekly from week 19 to week 38 post-randomisation, and if necessary, checking with a member of the ward team to ensure that it accurately reflects the participant’s behaviour. The MOAS is not always completed by the same research nurse/clinical support officer, so we are recording who has conducted each assessment.

The MOAS is a validated observer-rated measure that assesses the frequency and severity of aggressive incidents among people with ID over the past week (ICC = 0.93 [16]). The scale consists of four categories: verbal aggression, aggression against property, auto-aggression (against self), and physical aggression (against others). Each category will be scored using a 5-point scale (0 = no events within that category, 4 = most severe form of aggression within the category). The rater selects as many items as are appropriate. The items in each category are summed. The summed scores are multiplied by the severity weight for that category (verbal aggression × 1, aggression against property × 2, auto-aggression × 3, physical aggression × 4). The weighted scores are summed to obtain the total MOAS score, with a higher score indicating more aggressive behavior [16]. Thus, the primary outcome is a change in the MOAS score from baseline to week 19 post-randomisation.

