### Analysis of primary outcome

The aim of the primary analysis is to examine the effectiveness of art psychotherapy in reducing the frequency and severity of aggressive incidences compared to usual care, as measured by the change in MOAS score from baseline to week 19 post-randomisation. The distribution of the MOAS scores will be assessed graphically using histograms and the mean (SD) or median [IQR] of the change in score from baseline to week 19 will be tabulated overall and by trial arm (art psychotherapy versus usual care). The change of primary outcome from baseline to week 19 will be assessed graphically using a scatter plot.

The primary outcome analysis will be performed on an ITT basis. Initially, we will use a linear mixed-effect regression model [27, 28], with the week-19 MOAS score as the dependent variable and the randomisation group as the independent variable, adjusted for the baseline MOAS score, random effect of the variable indexing strata based on gender and diagnosis of psychosis. In addition, we anticipate potential clustering in the intervention arm due to therapists. We will examine this by the ICC from the linear mixed-effect model and if there is a considerable amount of heterogeneity in the primary outcome associated with therapists, we will adjust the effect estimate for the partial clustering due to therapists. For this, both partially homoscedastic and heteroscedastic regression models will be explored, and we will report the results as appropriate. The homoscedastic model assumes between-cluster variability is only present in the intervention arm and the individual level variation is the same in both arms. The heteroscedastic model assumes between-cluster variability is only present in the intervention arm but allows different individual level variation in intervention and control arms [29, 30]. From the initial model(s), we will present the estimated difference in MOAS score at week-19 for the intervention group compared to the control group with 95% CI.

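### The exploratory MOAS responder analysis counts participants at the floor of the scale as non-responders, and baseline MOAS is not among the planned effect modifiers

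*Protocol article*

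**What the plan says.** All references are to the protocol article.

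- **Inclusion criteria** accept a HoNOS item 1 score of 1 to 4 that may be current or historic. The item covers "overactive, aggressive, disruptive, or agitated behaviour/behavioural problems directed at others", which is wider than aggression. No MOAS level is required. **Exclusion criteria** rule out an item 1 score of 0 and give no time frame.
- **Primary outcome**: the MOAS "assesses the frequency and severity of aggressive incidents among people with ID over the past week". A category with no events scores 0, so the total can be 0 and cannot be lower.
- **Analysis of primary outcome**: the week-19 MOAS score is compared between arms, "adjusted for the baseline MOAS score, random effect of the variable indexing strata based on gender and diagnosis of psychosis". Baseline MOAS is a main effect only.
- **Subgroup analyses** (exploratory): "We will investigate whether the treatment effect varies by primary mental health diagnosis or level of learning disability using the LDSQ score". The models will "include an interaction term between allocation and primary mental health diagnosis and (in a separate analysis) between allocation and LDSQ score". Findings are also reported by age group, gender, ethnicity and diagnosis.
- The same section sorts therapy completers by change from baseline to 38 weeks into responders, neutral and deteriorators, first on the BSI and then on the MOAS. It compares the demographic and clinical profiles of responders and non-responders, and fits an allocation-by-respondence interaction.
- **Secondary objectives** include: "To explore patient characteristics and psychotherapeutic processes/mechanisms within interpersonal art psychotherapy that are influential to treatment".

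**The concern.** A responder profile is meant to show which patients benefit. If some participants start where improvement on the scale is impossible, they are classed as neutral or deteriorators whatever the therapy does. The profile then reports low baseline aggression as a mark of non-response, and a reader may take a property of the scoring rule for a clinical finding.

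The planned allocation-by-respondence interaction does not help. It is built on change after randomisation, so it carries the same artefact and is no substitute for a baseline modifier. The baseline interactions that are planned leave out baseline MOAS, although it is already collected and bears directly on the objective about influential patient characteristics. If the average effect is small, any examination of whether it differs by starting level would be post hoc.

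**Working it through.** **1. The floor in the responder rule.** The article can be read in two ways.

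- *Any improvement counts.* A participant at baseline 0 can only stay at 0 (neutral) or rise (deteriorator). Those at 1 to 4 can still improve.
- *Improvement must exceed a reliable-change threshold T.* Nobody with baseline below T can respond. The article does not give T. For illustration, take the SD of 10 (Sample size) and the ICC of 0.93 (Primary outcome; the type of ICC is not stated) as the reliability: T = 1.96 × 10 × √(2 × (1 − 0.93)) = 7.3 points.

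Either way, the low end of the baseline distribution is excluded from response by construction.

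**2. The plan's sample size.** Inputs from Sample size: difference 5, SD 10, correlation 0.25, two-sided 5%, power 80%. The residual SD is 10 × √(1 − 0.25²) = 9.68. Then n = 2 × (9.68 × (1.960 + 0.842) / 5)² = 58.9, so 59 per arm, as stated.

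**3. Dilution, as an illustration only.** Assume that a share p has zero effect and the rest gain 5 points. Neither assumption is in the article. SE = 9.68 × √(2/59) = 1.783, and power = Φ(5(1 − p)/1.783 − 1.96).

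| p | average effect | power at 59 per arm |
|---|---|---|
| 0% | 5.0 | 80% |
| 20% | 4.0 | 61% |
| 30% | 3.5 | 50% |
| 50% | 2.5 | 29% |

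The row for 20% agrees with Table 1 of the article, where an effect of 4 needs 92 per arm.

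The zero-effect assumption is extreme. With a correlation of 0.25, equal means and SDs and a linear relation, a control participant at baseline 0 is expected at (1 − 0.25) = 75% of the group mean at follow-up. If benefit scales with that expected score (also an assumption), the low group gains 0.75 × 5 = 3.75 points. The average effects at p = 20%, 30% and 50% are then 4.75, 4.63 and 4.38, with power of about 76%, 74% and 69%.

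**4. What an interaction could show.** Contrast an effect of 5 with an effect of 0 between two baseline groups, with share f in the low group: SE = 9.68 × √(2/(59(1 − f)) + 2/(59f)).

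| f | SE | 95% half-width | power |
|---|---|---|---|
| 20% | 4.46 | 8.7 | 20% |
| 30% | 3.89 | 7.6 | 25% |
| 40% | 3.64 | 7.1 | 28% |
| 50% | 3.57 | 7.0 | 29% |

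A continuous baseline term would differ somewhat, but these figures show the order of precision.

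**5. Regression to the mean at the other end.** Under the same assumptions as in step 3, a participant 10 points above the mean at baseline is expected to fall by 0.75 × 10 = 7.5 points without any treatment effect. That exceeds both the 5-point MCID and the illustrative T.

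**The case against.** The strongest counter-argument is that a within-person fall is not a treatment effect. The primary analysis compares week-19 scores between arms. A participant with one quiet week at baseline may be aggressive later under usual care, and therapy could prevent that. This stands: low baseline MOAS does not make a participant uninformative for the primary analysis, and the 5-point figure is the plan's overall difference ("we assumed a minimum clinically important difference (MCID) of 5 points on the MOAS scale"), not an effect confined to aggressive participants.

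A reader might infer three stronger claims, and the article supports none of them.

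- *Participants need have no current aggression.* The undated exclusion of a HoNOS score of 0 leaves this open. The two criteria conflict for someone with a historic score of 1 to 4 and a current score of 0.
- *A diluted result cannot be told from an ineffective therapy.* Baseline data will be summarised by arm with histograms, boxplots and ranges, and an interaction could be fitted afterwards. A pre-specified one would not settle the matter either.
- *Power falls to 61%, 50% or 29%.* This holds only under both assumptions in step 3.

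It can also be said that restricting the responder profile to high scorers selects for regression to the mean. That is true and should be stated in the report. It already affects the plan's own classification, however, so it is no reason to leave floor participants among the non-responders.

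**Conclusion.** The point holds in limited form. The MOAS responder classification misleads at the floor. The direction is certain; the size depends on how many completers start at 0 or below the threshold, which the article does not give. The absence of baseline MOAS from the exploratory modifiers is a smaller gap, worth closing because the variable is in hand and a stated objective calls for it. The expected gain is modest: power of about 20% to 29% and interval half-widths of about 7 to 9 points. The listed interactions are also exploratory, so low power alone is no reason to omit this one. Neither issue affects the validity of the primary ITT comparison.

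**What to change.** Leave the ITT primary analysis unchanged. Under Subgroup analyses:

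1. In the MOAS responder analysis, list participants at baseline 0, or below the reliable-change threshold if one is used, as a separate group unable to show improvement, not as non-responders. State the threshold, and note that regression to the mean inflates apparent response among high scorers.
2. Report by arm the number with baseline MOAS 0 and the number below 5. The second count also helps with the 5-point split under Responsiveness.
3. Pre-specify one exploratory allocation-by-baseline-MOAS interaction, with MOAS continuous, and state its low power and that it informs but does not settle whether a small effect reflects dilution.
4. Reconcile the HoNOS inclusion and exclusion criteria, and report which reading was applied at screening.

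The cost is a few sentences and no new data. The downsides are one more low-powered exploratory test and a smaller denominator for the MOAS responder profile. The change should be made before unblinded analysis.

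### The reliable-change categories are defined without the Reliable Change Index: as written, any improvement makes a responder and only an identical score is neutral

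*Protocol article*

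**What the plan says.** All of the relevant text is in the Protocol article under Subgroup analyses, which opens by stating "The following subgroup analyses will be exploratory only". The second paragraph there plans a reliable-change analysis restricted to therapy completers, defined as those who covered 5 of the 7 components, using the BSI PSDI.

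- Purpose: the RCI is described as a "psychometric criterion used to evaluate whether a change over time of an individual score" counts as statistically significant.
- First step: "Firstly, we will identify the RCI on the BSI from baseline (B) to 38 weeks follow-up (F"). No cut-off and no reliability coefficient is given.
- Classification: participants are "categorised as responders if they see improvement from B to F, neutral if their scores do not change, and deteriorators if their scores worsen". None of the three definitions mentions the RCI or any threshold.
- Extension: "We will repeat the process for MOAS score".
- Use: the three-level factor enters the primary model as an interaction with allocation, and the demographic and clinical profiles of responders and non-responders are compared.

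**The concern.** The RCI exists to separate change that exceeds measurement error from change that does not. A rule based only on the direction of the raw difference does not make that separation. The plan names the criterion and then defines its categories without it, so two analysts could follow the same text and report very different results.

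The outputs at stake are the percentages of responders and deteriorators and the comparison of their profiles. The profile comparison bears on the secondary objective about patient characteristics and therapeutic processes that influence treatment. If the groups are formed by the sign of the change, participants whose true state is the same are split by random variation, and the split could be published under the label of reliable change.

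This is not a matter of an article leaving detail to a fuller document. The Background section presents the paper as the detailed analysis plan, and the classification rule is stated in it. Where the authors intend a threshold elsewhere, they write one: the Responsiveness section classifies MOAS change by whether the 5-point MCID is reached.

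**Working it through.** **Inputs from the Protocol article.** PSDI SD 0.8, PSDI difference 0.5 and 59 evaluable participants per arm (Sample size); PSDI scored as the sum of the positive responses divided by their number (Secondary outcomes). The article gives no PSDI test-retest reliability, so r = 0.6 to 0.9 is assumed.

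**The plan's own PSDI figure.** No responder rate or RCI cut-off is stated. The only PSDI result is power above 90%. With n = 59 per arm, 0.5/(0.8 × √(2/59)) = 3.39, and Φ(3.39 − 1.96) = 0.924. At n = 75 it is 0.969. The figure reproduces, so 0.8 and 0.5 are used below.

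**Rule as written, no true change.** The change score is then symmetric about zero, so

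P(responder) = P(deteriorator) = (1 − tie rate)/2.

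*PSDI.* With no ties this is 50%. An illustrative 53-item simulation gave the values below. Its item model is assumed and its PSDI SDs were 0.37 to 0.56, below the planning value of 0.8, so it serves only to show the effect of ties.

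| Exact ties | Responders |
|---|---|
| 3% | 49% |
| 13% | 43% |
| 36% | 32% |

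*MOAS.* Suppose a share p0 scores zero at each time and all ties are zero–zero (p0 is assumed). If visits are independent, the tie rate is p0². If the same people score zero both times, it is p0.

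| p0 | Responders, independent visits | Responders, same people at zero |
|---|---|---|
| 0.3 | (1 − 0.09)/2 = 46% | (1 − 0.3)/2 = 35% |
| 0.5 | (1 − 0.25)/2 = 38% | (1 − 0.5)/2 = 25% |
| 0.7 | (1 − 0.49)/2 = 26% | (1 − 0.7)/2 = 15% |

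**Rule with an RCI threshold.** The cut-off is 1.96 × SD × √(2(1 − r)). With SD 0.8:

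| Assumed r | SE of difference | PSDI cut-off |
|---|---|---|
| 0.6 | 0.716 | 1.40 |
| 0.7 | 0.620 | 1.21 |
| 0.8 | 0.506 | 0.99 |
| 0.9 | 0.358 | 0.70 |

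With no true change and normal error, 1 − Φ(1.96) = 2.5% are responders, 2.5% deteriorators and 95% neutral. This does not depend on r, provided the r used is the right one.

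**In numbers of people.** If all 59 evaluable participants in the intervention arm were completers (an assumption), no true change and no ties would give 59 × 0.50 ≈ 30 responders under the written rule, against 59 × 0.025 ≈ 1.5 with the RCI.

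**With a true gain of 0.5 for everyone.** P(any improvement) = Φ(0.5/SE), and P(improvement beyond the RCI) = 1 − Φ(1.96 − 0.5/SE).

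| Assumed r | Any improvement | Beyond the RCI |
|---|---|---|
| 0.7 | 79% | 12% |
| 0.8 | 84% | 17% |
| 0.9 | 92% | 29% |

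The two readings of the rule therefore differ widely whether or not there is a true effect.

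**The case against.** The strongest reply is that the paragraph should be read in sequence. It announces reliable change, defines the RCI, says the RCI is identified first, and only then categorises. Identifying the RCI has no purpose unless the categories use it, so the natural intention is reliable improvement, no reliable change and reliable worsening. This has force. A reader might infer that the RCI will never be applied, and the text does not establish that. What it does establish is that the definitions, as they stand, carry no threshold. Even on the favourable reading the cut-off is open: assumed reliabilities of 0.6 to 0.9 move it between 1.40 and 0.70 PSDI points.

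A second reply is that half of completers being responders by noise alone is an upper bound. That is correct. It needs the literal rule, no true change and few ties, and a zero-heavy MOAS gives less.

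A third concerns the MOAS. A reader might infer that its RCI will be built on the reliability in the Primary outcome section, "over the past week (ICC = 0.93 [16"), and would be too lenient, because the Sample size section assumes only "a correlation of 0.25 between the baseline and post-treatment MOAS scores". The documents do not support this as an error. Nothing says 0.93 will enter an RCI. The 0.25 is a planning correlation over many weeks, so it may reflect genuine individual change as well as fluctuation.

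Finally, the analysis is exploratory, and neither the primary estimate nor the randomised PSDI comparison uses these categories. Adverse events are tabulated separately under Safety, so deteriorator is a score category and not a finding of harm. All of that stands and limits the consequence.

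**Conclusion.** The point holds as a defect in a stated rule. The three definitions contradict the reliable-change purpose given just before them, and followed literally they count trivial differences as response or deterioration. With no true change the written rule labels (1 − tie rate)/2 as responders: up to about 50% on the PSDI, and roughly 15% to 46% on the MOAS for assumed zero shares of 0.3 to 0.7. A 1.96 RCI gives about 2.5%. These figures rest on exchangeable visits, the tie rates shown and, for the 2.5%, normal error with the correct reliability. None is stated in the article.

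The damage is confined to the exploratory responder and deteriorator percentages, the interaction with response category and the profile comparisons. The primary analysis is unaffected.

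**What to change.** Rewrite the three definitions so that the threshold is explicit, with lower scores being better on both scales:

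- responder: improvement of at least the RCI;
- deteriorator: worsening of at least the RCI;
- neutral: absolute change smaller than the RCI;
- RCI = 1.96 × SD at baseline × √(2(1 − r)).

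State the SD and the source of r in advance, separately for PSDI and MOAS. For the MOAS, the week-to-week variability of the weekly scores in the usual-care arm would be one reasonable source of the error term. That is a preference, and curing the wording does not depend on it.

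The cost is a short change to the plan and minor programming. The downside is that fewer participants will be labelled responders. If the change comes after the analyst has seen outcome data, it should be reported as a deviation, as the Conclusion section already provides.

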## Discussion

This paper presents the detailed SHEAP for SCHEMA trial, which is a two-arm, parallel-group, single-blind, individually randomised controlled trial of effectiveness, comparing manualised interpersonal art psychotherapy to usual care. The main objective is to assess the effectiveness and cost-effectiveness of interpersonal art psychotherapy (compared to usual care) in reducing the frequency and severity of aggressive behaviour in adults in secure care. This SHEAP is aimed to evaluate the effect of intervention on primary and secondary outcomes with an adjustment for the pre-planned covariates in mixed effect linear regression models. We will analyse data on an intention-to-treat basis and use datasets generated by multiple imputations using chained equations to assess the effect of missing observations on the analyses if required. In addition, we will conduct a per-protocol analysis which will include only those participants who adhere to the intervention.

The SHEAP will minimise the risk of outcome reporting bias as having a predefined plan will minimise the risk of data-driven analyses. We strengthen our results by replacing missing observations with imputed values from multiple imputations by chained equations, facilitating calculation of unbiased estimates, standard errors and confidence intervals.

It is worth mentioning here that the proxy EQ-5D-3L and ReQoL-10 questionnaires completed by the ward staff at baseline, 19 and 38 weeks post-randomisation will be completed by a member of staff who is familiar with the participant’s general health; however, it may not always be completed by the same person, so we will record who has conducted each assessment. The variability in who completes the questionnaire could introduce measurement bias or inter-rater variability, which might affect the reliability and validity of the proxy EQ-5D-3L outcome. The ICC could be calculated to quantify the degree of agreement between nurses, and an exploratory sensitivity analysis could include the research nurse as a random effect in the primary analysis.

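### Week-38 responder status is used as a moderator of the week-19 MOAS effect, and the adherers-only per-protocol set has no control counterpart

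*Protocol article*

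**What the plan says.** The Subgroup analyses section of the protocol article opens by calling its analyses exploratory. It plans allocation interactions with two baseline variables, primary mental health diagnosis and LDSQ score. It then adds a responder analysis: "We will also conduct an analysis of reliable change for therapy completers (5 out of 7 components of art psychotherapy"), based on the change in BSI PSDI from baseline (B) to 38 weeks (F). The classification rule reads "Participants will be categorised as responders if they see improvement from B to F, neutral if their scores do not change", with worsening scores classed as deterioration. The same process is repeated for MOAS. Finally the primary analysis, a model for MOAS at week 19, is rerun to "additionally include an interaction term between allocation and therapy respondence (responder/neutral/deteriorators").

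The Discussion adds a second analysis conditioned on what happens after randomisation: "we will conduct a per-protocol analysis which will include only those participants who adhere to the intervention". Analysis population says this will be done where applicable. Adherence means completing at least 5 of the 7 therapy components (Adherence section). Controls are offered the therapy only once their participation has ended (Trial design).

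**The concern.** A moderator has to be fixed before treatment can act on it. Respondence is not: it is built from the participant's own later outcome, in one version on the primary scale itself, and is complete only 19 weeks after the week-19 endpoint. People who do well at week 38 tend to have done well at week 19 whatever they received. Sorting on that status sorts on the outcome.

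The text also leaves open who is classified. The references to therapy completers and therapy respondence point to the intervention arm only. The general reference to participants, and an interaction with allocation, point to both arms. The two readings fail in different ways.

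The per-protocol set has a related fault. Adherence is defined by therapy components that controls cannot complete during the trial, so a set limited to adherers contains no controls. If all controls are kept, completers, who are a selected group, are compared with an unselected arm.

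At stake is the exploratory account of who benefits and what full therapy achieves. One secondary objective is to explore patient characteristics and processes that influence treatment.

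**Working it through.** **Inputs from the document (Sample size).** MOAS difference Δ = 5; SD = 10 in each arm; ρ = 0.25 for baseline with follow-up MOAS; 80% power, two-sided 5%, 59 evaluable per arm.

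**Reproducing the plan's figure.** n = 2 × [SD × (z₀.₉₇₅ + z₀.₈₀)/Δ]² × (1 − ρ²) = 2 × [10 × (1.960 + 0.842)/5]² × (1 − 0.0625) = 58.87, so 59 per arm, as stated. 59/0.8 = 74 against the stated 75, a difference of one.

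**Is the interaction estimable if only the therapy arm is classified?** The model has six columns: intercept, allocation, two status indicators and two products. With no classified controls, each product equals its status indicator. The rank is 4, so the interaction cannot be separated from the main effect of status. If controls are instead left with missing status, they drop out and allocation is constant.

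**Simulation.** 59 per arm; MOAS normal with SD 10; correlation of baseline with each follow-up 0.25; ANCOVA of week-19 MOAS on baseline; 4,000 trials per setting. A responder has any improvement from baseline to week 38. The week-19/week-38 correlation is not in the document, so it is assumed at 0.25, 0.5 and 0.7. The last column assumes a 5-point effect at both weeks; the others assume none. Negative values favour therapy.

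| Assumed correlation | Therapy responders vs all controls | Significant false benefit | Therapy non-responders vs all controls | Interaction, both arms classified (rejection) | Effect among responders, both arms classified, true effect −5 |
|---|---|---|---|---|---|
| 0.25 | −1.4 | 9% | +1.4 | 0.0 (5%) | about −4.4 |
| 0.5 | −3.2 | 31% | +3.2 | 0.0 (5%) | −3.9 |
| 0.7 | −4.7 | 59% | +4.7 | 0.0 (5%) | about −3.4 |

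Under the null, the ITT model gave a mean difference of about 0 and about 5% rejection.

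The last column shrinks because therapy moves some participants with a poorer prognosis over the responder line, so treated and control responders are no longer alike. The shrinkage needs an effect that persists to week 38; without one, status would be unrelated to allocation.

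For BSI-defined status, responders against controls gave −2.3 points and 19% false benefit when BSI change was assumed to correlate 0.3 with the week-19 MOAS residual. With zero correlation there was no bias.

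**Per-protocol: completers against all controls, no true effect.** The completion rate p and its correlation c with a better outcome are both assumed. The residual SD is 10 × √0.9375 = 9.68, and the expected bias is −c × 9.68 × φ(z_p)/p. At p = 0.75, φ(0.674)/0.75 = 0.424:

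- c = 0.3: −0.3 × 9.68 × 0.424 = −1.2 (simulated −1.3; 9.5% falsely significant for benefit against 2.5% nominal)
- c = 0.5: −2.1 (simulated −2.0; 18.5%)
- c = 0: 0
- c = −0.3: +1.2, a false harm

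At c = 0.3, simulated bias was −1.9 with 60% completion and −0.6 with 90%.

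**The responder threshold.** The plan introduces the Reliable Change Index as the test of individual change, but its category wording speaks only of improvement or no change. Taking the MOAS ICC of 0.93 (Primary outcome section) as the reliability, which the document does not confirm, the threshold is 1.96 × √2 × 10 × √(1 − 0.93) = 7.3 points. This is above the 5-point MCID, so the wording matters to who is classed as a responder.

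**Limits.** Scores are normal, therapist and stratum effects are left out, status has two levels instead of three, and the therapy-arm-only reading is not restricted to completers. The results show direction and scale only.

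**The case against.** A reader might infer that the planned interaction will itself show benefit where there is none. The document does not support that. On one reading the interaction cannot be estimated; on the other it is centred on zero with about 5% rejection under the null. The 9% to 59% false-benefit rates belong to a responders-versus-controls contrast that the plan does not name, and non-responders show equal and opposite harm. They describe what would be left after the interaction drops out of a therapy-arm-only model.

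A reader might also take respondence to exist only in the therapy arm. That is certain for adherence, but only one reading for respondence, since BSI and MOAS are scheduled for everyone at baseline and week 38 (Table 2).

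It could further be said that the section is labelled exploratory, that the primary analysis is ITT, and that baseline moderators are already planned. All of this stands and limits the consequence. It does not make the respondence model interpretable.

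Reading the rule as any improvement, however small, is uncharitable, because the plan says it will identify the RCI before classifying. The wording needs tightening; it is not evidence that the RCI will be ignored.

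On per-protocol, the assumed completion rates and correlations have no source in the document, and the bias vanishes if completion is not prognostic. So it cannot be said that the analysis will overstate benefit. What stands is that a set of adherers only has no defined control group.

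**Conclusion.** The concern holds in a limited form. Change to week 38 is not a valid moderator of a week-19 effect, and neither reading of the text gives a usable analysis. With only therapy completers classified, the interaction is not estimable, and the remaining contrast is biased by about −3.2 MOAS points at an assumed correlation of 0.5 (−1.4 to −4.7 over 0.25 to 0.7). With both arms classified, there is no false interaction under the null, but a true uniform 5-point effect lasting to week 38 appears as about 3.4 to 4.4 points among responders and says nothing about who benefits.

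The adherers-only set is also badly specified. Comparing completers with all controls gave −2.0 to +1.2 points under the null at 75% completion, with the sign depending on how completion relates to outcome.

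The ITT primary conclusion is not affected. This is a correction to exploratory and supplementary analyses, below the level of something that must be fixed for the trial's main result to stand.

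**What to change.** 1. Delete the allocation-by-respondence interaction.
2. Classify participants in both arms by the RCI threshold, word improvement and deterioration as change beyond that threshold, and state the reliability coefficient used for each scale. Compare the three categories by arm as an exploratory ITT outcome at week 38.
3. Keep effect-modifier analyses to baseline variables, as already planned for diagnosis and LDSQ score. Responder profiles may still be described, without a claim about treatment effect.
4. Replace or supplement the adherers-only per-protocol analysis with a complier-average causal effect for completing at least 5 of 7 components, using allocation as the instrument and keeping all randomised participants.

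The cost is revised analysis-plan wording and a few lines of Stata; no new data are needed. The complier-average estimate needs the exclusion restriction, which is doubtful if people who complete fewer than five components still gain something. Its confidence interval is also wider, roughly 1/0.75 = 1.33 times the ITT width at an assumed 75% completion.
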